## Abstract

**Background::**

Cough is a common symptom that occurs in 25% of patients after lung cancer surgery. It might last a long time and degrade the quality of life of patients. Maekmoondong-tang (Bakumondo-to in Japanese or Mai-Men-Dong-Tang in Chinese) is a herbal medicine which has been widely used for respiratory diseases with cough in Korea, China, and Japan.

**Aims::**

The aim of the present study is to evaluate the efficacy and safety of Maekmoondong-tang for postoperative cough in patient with lung cancer.

**Methods/Design::**

This study is a randomized, double-blind, placebo-controlled, multicenter trial of Maekmoondong-tang. A total of 96 participants will be enrolled and allocated to 2 parallel groups: the Maekmoondong-tang group and the placebo group from 5 university hospitals. The participants will be administered either Maekmoondong-tang or a placebo 3 times a day for 4 weeks. The primary outcome measurement is the change in the Leicester Cough Questionnaire (LCQ) score. The secondary outcome measurements are the changes in the cough visual analog scale and Yin Deficiency Scale. The participants will visit 4 times in total for 4 weeks of trial period.

**Discussion::**

The present study will be the first multicener study to evaluate the efficacy and safety of Maekmoondong-tang for postoperative cough in patient with lung cancer surgery. The results of this study will provide a new treatment for cough using herbal medicine and will be a reference for planning clinical trial of herbal medicine in patient with cough.

## Introduction

1

In 2015, cancer was responsible for 8.8 million deaths and of these, 1.69 million of them died from lung cancer.^[1]^ In Korea, lung cancer is the fourth most common cancer after thyroid cancer, gastric cancer, and colon cancer in 2014 and the 5-year cancer relative survival rates for the period 2010 to 2014 was 25.1%, an improvement of more than 5% over the period 2006 to 2010.^[2]^ It is reported that cough occurs in about 25% of patients after lung cancer surgery.^[3]^ Postoperative cough is known to be related to mediastinal lymph node resection, elevation of the diaphragm, loss of lung volume, and gastroesophageal reflux.^[4]^ Postoperative cough may last a long time and degrade the quality of life of patients, but there is not much research on this subject.^[5]^

Maekmoondong-tang (MMDT, Bakumondo-to in Japanese or Mai-Men-Dong-Tang in Chinese) is an herbal medicine approved by Ministry of Food and Drug Safety (MFDS). There are preclinical studies, clinical studies, and literature evidence that MMDT is effective in treating cough. Synopsis of Prescription of the Golden Chamber (Jin Gui Yao Lue) in which the MMDT was first introduced, records that MMDT treats cough with qi reflux and discomfort in the throat. Treasured Mirror of Eastern Medicine (Dongeuibogam) records that MMDT treats dyspnea due to fire which means serious cough caused by phlegm-fire or fire of thoroughfare vessel surging to lung. These records of classics of traditional medicine shows that MMDT is a herbal medicine that is effective against various respiratory diseases whose chief complaint is cough. In Korean medicine clinic, MMDT has been widely used for respiratory diseases with cough such as chronic bronchitis, bronchiectasis, and chronic laryngopharyngitis.^[6]^ Previous studies have shown that MMDT significantly relieves a cough and improves the quality of life in patient with cough after lung cancer surgery than the control group.^[7,8]^ It is also reported that MMDT alleviates cough in patients with chronic obstructive pulmonary disease (COPD).^[9]^ A systematic review of MMDT for cough reported that MMDT reduced the cough severity by 74% compared to the conventional cough medicines in various diseases.^[10]^ In addition to cough, the efficacy of MMDT in lung cancer itself, in which the tumor response rate was increased and the side effect rates were decreased in combination with EP regimen, has also been reported.^[11]^ There were several preclinical studies of MMDT on cough. MMDT attenuates airway hyperresponsiveness induced by ozone and has bronchodilating action by reducing the tension of bronchial smooth muscle and increasing cyclic AMP.^[12,13]^ MMDT also supressed the cough reflex caused by mechanical and chemical stimulations.^[14]^

In Korean medicine theory, cough is one of the symptoms due to yin deficiency which is a pathological change characterized by diminished moistening.^[15]^*Liriope Tuber* which is a primary constituent herb of MMDT has an effect of tonify yin and moisten the lung,^[16]^ therefore MMDT is expected to be effective for cough due to yin deficiency.

Many studies have been conducted for the improvement of quality of life and symptom management in patient with cancer lately. However, study for cough after lung cancer surgery is rarely conducted relative to its frequency.

The aim of the present study is to evaluate the efficacy and safety of MMDT for cough after lung cancer surgery. For this, a randomized, double-blind, placebo-controlled, multicenter trial will be conducted.

## Materials and methods

2

### Study design

2.1

A randomized, double-blind, placebo-controlled, multicenter trial will be conducted at the Korea University Guro Hospital, Korea University Anam Hospital, Korea University Ansan Hospital, Gangnam Severance Hospital, and Inje University Ilsan Paik Hospital. Participants who meet the eligibility criteria will be enrolled and randomly allocated to MMDT group or placebo group. Each participants will visit the trial institutions 4 times for 4 weeks. At each visit, participants will be examined for signs and symptoms related to cough, quality of life and safety. The study flow chart is shown in Figure 1. Protocol modifications are not expected; however if they are necessary, any changes in the protocol will be announced to the all investigators via a conference. The management, analysis, and reporting of study will be conducted independently by the study investigators.

**Figure 1 F1:**
[figure not shown]
Study flowchart.

### Participants

2.2

The inclusion criteria are as follows:20 years or older;patients undergone segmentectomy or lobectomy for lung cancer within 1 month;patients who do not or poorly respond to one week administration of common antitussive agents;Eastern Cooperative Oncology Group (ECOG) performance status 0 to 2;participants who are willing and able to give informed consent for participation in the study.

The exclusion criteria are as follows:patients undergoing adjuvant chemotherapy;patients who have been diagnosed with acute respiratory disease within 1 month;patients who have been diagnosed with bronchial asthma or bronchiectasis within 1 year;patients taking angiotensin converting enzyme inhibitor;patients diagnosed pneumonia with a positive chest x-ray;patients with infection suspected to the cause of cough in sputum cultures;patients with pseudoaldosteronism;participants who have known prior hypersensitivity to any investigational product component;patient with acute or chronic infections requiring treatment (active hepatitis A, B, and C viruses, human immunodeficiency virus, tuberculosis);pregnant or lactating females;women of childbearing potential;patients who do not agrees to use effective means of contraception and not to donate sperm during the trial and up to 1 month after final administration;patient who participated other clinical trials of medicine or medical devices within 1 month; andindividuals who are judged inappropriate for the study by investigator

The withdrawal criteria are as follows, and the reasons of the withdrawal will be clarified in the case report forms (CRFs):participants who do not follow the instructions of investigators;occurrence of significant protocol violations;occurrence of a serious adverse event (AE);investigator's decision to terminate the process for the sake of the participant's health; andparticipant's withdrawal of consent

The participants who are withdrawn from the study after allocation will be followed for outcome measurements as far as possible.

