### Sample size

2.4

Sample size calculation was conducted based on previous study that reported efficacy of MMDT on prolonged cough after lung cancer surgery.^[7]^ There was no study evaluated efficacy of MMDT using Leicester Cough Questionnaire (LCQ) in patients with lung cancer, thus, the changes of Short-From 36 (SF-36) score of the previous study were transformed to LCQ score. The mean differences of LCQ scores were hypothesized to be 8.40 and 5.52 in MMDT group and placebo group, respectively, and the standard deviation was hypothesized to be 3.45. The following formula was used to calculate the sample size. The calculation was performed using 95% power, and a 5% significance level 
[figure not shown]

Considering a drop-out rate of 20%, the needed sample size is approximately 48 participants for each group. Therefore, a total of 96 participants are needed for the present study.

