## Discussion

3

Cough is a symptom of many respiratory diseases such as tonsillitis, laryngitis, pharyngitis, lung cancer, asthma, bronchitis, pneumonia, and tuberculosis. A systematic review reported that several herbal medicines have positive effect on cough in patient with childhood cough variant asthma.^[19]^ However, that study only evaluated the efficacy of combination treatment of herbal medicines and conventional therapies, and excluded the patients with serious respiratory disease including chronic obstructive pulmonary disease and lung cancer. There are several clinical trials to investigate efficacy of herbal medicine for cough in patient with cough variant asthma, postinfectious cough, and allergic asthma.^[9,20,21]^ Although previous study showed that MMDT can improve chronic cough after lung cancer surgery, that study had a limitations of small and single-centre trial.^[7]^ A study protocol for the treatment of chronic dry cough using MMDT has already been published^[22]^; however, the present study has several distinctive features of relatively large scale, multicenter trial for patients with lung cancer. The present study is the first multicenter, randomized, controlled trial for evaluating the efficacy of MMDT in Korea. The results of this study might provide a new treatment for postoperative cough in patient with lung cancer surgery. We expect that the present study protocol will serve as a reference for planning further clinical trials to treat cough using herbal medicines.

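### The trial enrols cough within 1 month of lung resection but is sized on an effect from prolonged or chronic cough; state the assumption, match the conclusion to those enrolled, and adjust for days since surgery

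*Protocol article*

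**What the plan says.** Protocol article, section 2.2 (Participants), sets two inclusion criteria that define the cough population. One is on time: "patients undergone segmentectomy or lobectomy for lung cancer within 1 month". The other is on response to treatment: "patients who do not or poorly respond to one week administration of common antitussive agents". Neither sets a minimum duration or severity of cough.

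The aim in the Introduction has no limit on duration: "The aim of the present study is to evaluate the efficacy and safety of MMDT for cough after lung cancer surgery". The Introduction motivates the work partly by persistence: "Postoperative cough may last a long time and degrade the quality of life of patients".

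Section 2.4 (Sample size) rests on a "previous study that reported efficacy of MMDT on prolonged cough after lung cancer surgery". Its SF-36 changes were converted to LCQ changes of 8.40 (MMDT) and 5.52 (placebo), with SD 3.45. The Discussion, citing the same reference, says that a "previous study showed that MMDT can improve chronic cough after lung cancer surgery", and expects the present results to offer a treatment for postoperative cough in general.

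Section 2.12.1 (Efficacy assessment) fixes the primary comparison as an independent t-test on the change from baseline (Visit 2) to Visit 4, without covariates.

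**The concern.** The patients enrolled are described by time since surgery, at most 1 month. The patients behind the planning effect are described by persistence of cough. These appear to be different populations, and the document does not say why a difference seen in one should hold in the other. Three things follow.

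- **Transportability.** The whole sample size depends on the 2.88-point difference. If early cough settles more on its own than prolonged cough, both arms improve and the gap between them may narrow. The placebo arm is already assumed to gain 5.52 points on a scale from 3 to 21, that is 5.52 / 18 = 31% of its range.
- **Scope.** The Discussion notes that the earlier study was small and single-centre and presents this trial as the larger multicentre one. A reader could take a positive result as confirmation in chronic cough, which the entry criteria do not secure.
- **Precision.** Patients may enter at quite different points of surgical recovery. If LCQ change depends on time since surgery, that variation goes into the error term of an unadjusted t-test.

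**Working it through.** **1. The plan's own figure.** Inputs from section 2.4: δ = 8.40 − 5.52 = 2.88, SD = 3.45, power 95%, significance level 5%, drop-out 20%. Allocation is 1:1 (section 2.5). The readable text does not state whether the test is one- or two-sided, so both were tried.

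n per group = 2 × [SD × (z for α + z for power) / δ]²

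- Two-sided: 2 × [3.45 × (1.960 + 1.645) / 2.88]² = 37.3, rounded up to 38. Then 38 / 0.80 = 47.5, rounded up to **48**, as stated.
- One-sided: 31.1, rounded up to 32, then 32 / 0.80 = 40, which does not match.

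The arithmetic is correct under a two-sided test. Only the source of δ is in question.

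**2. The populations side by side.**

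| Place | Population described |
|---|---|
| Section 2.2 | Resection within 1 month, poor response to one week of antitussives, no cough duration stated |
| Introduction (aim) | Cough after lung cancer surgery, no duration |
| Section 2.4 (source of δ) | Prolonged cough after lung cancer surgery |
| Discussion (same source) | Chronic cough after lung cancer surgery |
| Discussion (expected conclusion) | Postoperative cough, no time limit |

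The document defines neither 'prolonged' nor 'chronic', and does not give the earlier study's entry window.

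**3. What a smaller difference would cost.** The document gives no effect for early cough, so the fractions below are assumptions. SD is held at 3.45 with 38 evaluable per group.

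Power = Φ(δ / [SD × √(2/38)] − 1.96), where SD × √(2/38) = 0.791.

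| Share of planned δ | δ | Power | Per group for 95% power, before / after 20% drop-out |
|---|---|---|---|
| 100% | 2.88 | 95% | 38 / 48 |
| 75% | 2.16 | 78% | 67 / 84 |
| 60% | 1.73 | 59% | 104 / 130 |
| 50% | 1.44 | 44% | 150 / 188 |

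**4. Spread of time since surgery.** Assume that antitussives may start straight after surgery, that a month is 30 days, and that there is no gap between enrolment and Visit 2. Baseline then falls between about day 7 and day 30. Adding 28 days of treatment puts Visit 4 between about day 35 and day 58. The visit schedule is in a figure and a table that cannot be read here, so these are rough bounds.

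**5. What adjustment could gain.** If days since surgery correlate ρ with LCQ change within arms, the residual SD is 3.45 × √(1 − ρ²), and the n of 37.3 is multiplied by (1 − ρ²). The values of ρ are assumptions.

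- ρ = 0: SD 3.45, no gain. With 76 evaluable patients, error degrees of freedom fall from 74 to 73.
- ρ = 0.3: SD 3.29, n = 37.3 × 0.91 = 33.9.
- ρ = 0.5: SD 2.99, n = 37.3 × 0.75 = 28.0.

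**The case against.** The strongest case against is that the trial is consistent with its stated purpose. The aim and expected conclusion concern postoperative cough, and the enrolled patients have it. The remark that such cough may last a long time describes burden; it does not define a target population, and treating early does not conflict with it. This stands. A reader might infer that the trial cannot support the claim it is built on, but the document does not bear that out.

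A reader might also infer that persistent cough is the one population the trial shuts out. That is not shown either. The criterion limits time since surgery, not duration of cough, and none of the listed criteria bars a patient solely because the cough began before the resection. What can be said is that overlap with a prolonged-cough population is not guaranteed.

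Third, varying time since surgery does not bias the result. Randomisation balances it in expectation, and the concurrent placebo arm absorbs recovery common to both groups. This also stands; only precision is affected.

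Fourth, the earlier study is not at hand, so the size of any mismatch is unknown. This is true and limits the point to an unstated assumption.

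Finally, covariate adjustment is often left to the analysis plan. Here, however, the protocol itself names an unadjusted t-test, so it is fair to comment on that choice. The t-test is not an error; adjustment is a low-cost improvement on it.

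**Conclusion.** The point holds as one of scope, transportability and precision. The effect that sizes the trial is borrowed from cough described as prolonged or chronic and applied, without comment, to patients within 1 month of resection. The 48 per group is arithmetically right, and the randomised comparison is valid for the patients enrolled.

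The consequence for power cannot be fixed from the document. On the illustrative range it falls from 95% to between 78% and 44% if the true difference is 75% to 50% of 2.88 with SD unchanged; if the effect carries over in full, nothing is lost. That early recovery depends on days since surgery is plausible but not shown, so the gain from adjustment may be nil or worthwhile. The findings do not call for a change to the eligibility window, which is the sponsor's choice.

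**What to change.** 1. **Section 2.12.1:** replace the unadjusted t-test of LCQ change with a linear model (ANCOVA) containing treatment group and, as a pre-specified covariate, days from surgery to Visit 2. The operation date is already needed to check eligibility, so no new data are collected. The cost is about one degree of freedom; the benefit depends on how prognostic time since surgery proves to be.
2. **Section 2.4:** state that the 2.88-point difference is assumed to carry over from prolonged cough to cough within the first month after resection, and give the reason. This takes a sentence or two and leaves the sample size unchanged.
3. **Sections 2.2 and 2.4 and the Discussion:** reconcile the descriptions of the target population, and word the conclusion for antitussive-refractory cough within 1 month of segmentectomy or lobectomy. The cost is a narrower claim.

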### Recruitment

2.3

Participants will be recruited through 2 routes. Patients who visit the trial institutions and fulfil the eligibility criteria will be recommended by the investigators. Patients who see the trial poster on bulletin boards of the institutions will contact the investigators voluntarily. Written informed consent will be obtained from all participants prior to enrolment by the investigators.

### Sample size

2.4

Sample size calculation was conducted based on previous study that reported efficacy of MMDT on prolonged cough after lung cancer surgery.^[7]^ There was no study evaluated efficacy of MMDT using Leicester Cough Questionnaire (LCQ) in patients with lung cancer, thus, the changes of Short-From 36 (SF-36) score of the previous study were transformed to LCQ score. The mean differences of LCQ scores were hypothesized to be 8.40 and 5.52 in MMDT group and placebo group, respectively, and the standard deviation was hypothesized to be 3.45. The following formula was used to calculate the sample size. The calculation was performed using 95% power, and a 5% significance level 
[figure not shown]

Considering a drop-out rate of 20%, the needed sample size is approximately 48 participants for each group. Therefore, a total of 96 participants are needed for the present study.

### Randomization and allocation

2.5

The enrolled participants will be randomized using random numbers generated by computer at an independent centre, Institute of Safety, Efficacy and Effectiveness Evaluation for Korean Medicine (ISEE). The study participants will be assigned to one of 2 groups with a 1:1 allocation ratio in blocks of 4 by investigators in each trial institutions. The randomization table will be kept in an opaque sealed envelope and maintained by the ISEE during the trial period. The randomization table should be opened according to Standard Operating Procedures (SOPs).

### Blinding

2.6

A researcher not involved in recruitment, intervention or outcome assessment will handle the randomization. Therefore, both the investigators and the participants will be blinded for assignment of the investigational drugs. The investigational products will be manufactured and labeled at the Hanpoong Pharm & Foods Co, Ltd, a pharmaceutical company.

### Treatment protocol

2.7

The participants will receive MMDT or a placebo drug for 4 weeks. They will take 3 grams of granules by mouth with water 3 times a day before or between the meals for 4 weeks. The daily dose and usage follow the recommendation of the MFDS on MMDT. The participants will be required to return any remains of drug for calculating compliance. The participants will be prohibited to receive other additional treatment for cough during the trial.

### Interventions

2.8

Hanpoong Pharm and Foods Co., Ltd. produces the MMDT and placebo according to Korea Good Manufacturing Practice (KGMP) standards. The MMDT is a light brown-colored granuels, and it consist of 3.33 g *Liriope Tuber*, 1.67 g *Pinellia Tuber*, 3.33 g *Oryzae Semen*, 1 g *Zizhyphi Fructus*, 0.67 g *Ginseng Radix Alba*, 0.67 g *Glycyrrhizae Radix et Rhizoma*. The placebo is made of corn starch, lactose hydrate, citric acid hydrate, caramel colorant and ginseng flavor powder, and it is similar in appearance, shape, weight, taste, and color to the MMDT.

### Primary outcome measurement

2.9

The primary outcome in the present study is the change in the LCQ score between the baseline (Visit 2) and after the treatment (Visit 4). The LCQ is a valid, repeatable cough-specific quality of life questionnaire consists of 19 items, each rated on a 7-point Likert scale.^[17]^ Korean version of the LCQ also has been validated its concurrent validation, internal consistency, repeatability, and responsiveness.^[18]^ The total score of LCQ is 3 to 21, and a higher score means a better quality of life. The LCQ will be measured at visit 2, 3, and 4.

### Secondary outcome measurement

2.10

Secondary outcome measurements include the changes in the cough visual analog scale (VAS) and Yin Deficiency Scale (YDS). The study participants will mark a 100-mm linear VAS with 0 representing “no cough’ and 100 representing “worst cough.” YDS is a validated questionnaire measuring yin deficiency, consists of 27 items, each rated on a 7-point Likert scale.^[15]^ The cough VAS and YDS will be measured at visit 2, 3, and 4. The study schedule is detailed in Table 1.

**Table 1 T1:**
[figure not shown]
Study schedule of the Maekmoondong-tang study.

### Safety outcomes

2.11

All variables related to the participants’ safety including vital signs, physical examination, hematologic test, biochemical test, and urine test will be documented on the CRFs at every visit. Any AEs that occur after taking investigational drug will be documented on the CRFs. If the AE is severe and related to the investigational product, the participant will be withdrawn from the study, and the appropriate treatment and reimbursement will be provided to them.

